#### Secondary endpoints

BL during recipient hepatectomyTime from skin incision to end of hemostasis after hepatectomyTime from skin incision to end of skin closureHemodynamic status during surgery: Data on the mean arterial pressure and central venous pressure (CVP) will be obtained at the beginning of hepatectomy after incision and adhesiolysis.Coagulation state: International normalized ratio (INR), partial thromboplastin time (PTT), and platelet counts of patients will be recorded pre- and postoperatively until postoperative day (POD) 10.Hemoglobin (Hb) level: Hb levels of patients will be recorded pre- and postoperatively until POD 10.The number of units of packed red blood cells (PRBC) transfused during surgeryThe number of fresh frozen plasma (FFP) units transfused during surgeryThe number of platelet units transfused during surgeryPostoperative PRBC and FFP transfusion until POD 10Postoperative bleeding: Postoperative hemorrhaging until POD 10 will be recorded and classified as defined by Dindo et al. [21].Postoperative morbidity: Postoperative morbidity will be recorded and classified as defined by Dindo et al. [21].Retransplant rateConversion rate to alternative methods during recipient hepatectomy in LS and USD groups

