#### Randomization protocol

Sixty-nine LT recipients are expected to be randomized into three groups of at least 23 patients each:LS groupUSD groupControl group, using conventional bipolar coagulation devices, surgical suture ligatures, and surgical clips (or any dissecting/coagulating device other than LS)

Randomization will be performed using the “block randomization” method. Each block will contain multiple balanced combinations of the three groups: LS, USD, and control. Blocks will be randomly chosen (using simple randomization software with Excel® [Microsoft, Redmond, WA, USA]), and assignment of the participants to the respective groups will be determined. Randomization will be performed at any time between the inclusion of the patients according to the above-listed inclusion criteria and the beginning of recipient hepatectomy. Randomization will be performed by a member the clinical trial center (Klinisches Studien Zentrum [KSC]) of the surgical department of the University Hospital Heidelberg who is not otherwise involved in the trial. Afterward, the staff will personally inform the responsible surgeon about the treatment group to which the patient has been randomized.

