#### Statistical design

Dichotomous data and counts will be presented as frequencies. Continuous data will be presented as mean with SD or as median value with a range. Statistical interpretation of the data includes multiple *t* tests with Bonferroni correction for parametric data (including BL) and the Kruskal-Wallis test for nonparametric data. The chi-square test will be used for categorical data. The significance level will be set at alpha ≤ 0.05 (after a Bonferroni adjustment when applicable) representing 95% confidence.

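### Graded bleeding and morbidity would, on the plain reading, get a chi-square test that ignores grade order; a rank test is also named, and the protocol does not say which applies (minor)

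*Protocol article*

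**What the plan says.** All places are in the protocol article.

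- **Secondary endpoints**, on bleeding: "Postoperative hemorrhaging until POD 10 will be recorded and classified". On morbidity: "Postoperative morbidity will be recorded and classified". Both use the same cited grading system. The article does not list the grades, and it does not say whether the arms are compared by grade or by any event against none.
- **Statistical design**, description: "Dichotomous data and counts will be presented as frequencies". Continuous data have their own summary rule. Ordered categories are not mentioned.
- **Statistical design**, tests: t tests with Bonferroni correction for parametric data, "the Kruskal-Wallis test for nonparametric data", and then "The chi-square test will be used for categorical data". No test is tied by name to bleeding or morbidity.
- **Randomization protocol**: patients are "randomized into three groups of at least 23 patients each".

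**The concern.** A recorded class is categorical data in ordinary usage. The description rules point the same way: means go with t tests, medians with Kruskal-Wallis, and frequencies with chi-square. Read like that, two outcomes recorded by severity go to a test that does not know one grade is worse than another. If a device moved patients consistently towards milder or more severe complications, that test would use only part of the information collected.

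If the section is instead read as leaving the choice between chi-square and Kruskal-Wallis open, the test for two named endpoints could be chosen after the results are seen. One clarifying sentence settles both readings.

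**Working it through.** **Nothing to reproduce.** The protocol states no power for the graded endpoints. Its sample size calculation concerns total blood loss only and is not used here, apart from the 23 patients per arm.

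**Step 1: the test ignores order.** For a table of arms by grades, the Pearson statistic is the sum over cells of (observed − expected)² / expected. Reordering the grade columns leaves the sum, the degrees of freedom and the p-value unchanged.

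**Step 2: the cells are thin.** With no effect, the expected count in a level with proportion p is 23 × p. It is below 5 when p < 5/23 = 0.217. The assumed control distributions, from no complication to the worst level, are:

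- A (morbidity, 8 levels): .15, .10, .30, .10, .15, .10, .05, .05. Seven of 8 levels fall below 5.
- B (morbidity, 6 levels): .15, .10, .30, .25, .15, .05. Four of 6.
- C (morbidity, 6 levels): .30, .15, .25, .15, .10, .05. Four of 6.
- D (bleeding, 6 levels): .60, .05, .10, .20, .03, .02. Five of 6.

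So roughly two thirds or more of the expected counts are small. In simulation with no effect, the chi-square test then rejects in 2.5 to 3.9% of trials at a nominal 5%, so it is conservative.

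**Step 3: power for one device against control.** The device arm is shifted towards milder grades by a common odds ratio: at every cut of the scale, the odds of lying above it are divided by that ratio. Example for D at an odds ratio of 3: the chance of any bleeding is 0.40, odds 0.40/0.60 = 0.667; divided by 3 this is 0.222, so the chance is 0.222/1.222 = 0.18.

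Settings: 23 against 23, 40,000 simulated trials per scenario, two-sided alpha 0.05. The three tests are Pearson chi-square on the full grade table, Pearson chi-square after one cut between the third and fourth levels, and the tie-corrected Wilcoxon rank-sum test. Results at an odds ratio of 3:

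| Distribution | Chi-square, full table | Chi-square, one cut | Wilcoxon | Wilcoxon minus full table |
|---|---|---|---|---|
| A | 19.8% | 40.0% | 53.5% | 33.7 points |
| B | 26.1% | 39.3% | 52.6% | 26.5 points |
| C | 25.4% | 31.7% | 51.9% | 26.5 points |
| D | 16.4% | 27.6% | 38.0% | 21.6 points |

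The rank test has 2.0 times (52.6/26.1) to 2.7 times (53.5/19.8) the power of the full-table chi-square. Collapsing the scale to one cut recovers part of the loss.

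**Step 4: other effect sizes and alpha.**

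| Odds ratio, alpha | Chi-square, full table | Wilcoxon |
|---|---|---|
| 2, 0.05 | about 7–12% | about 19–25% |
| 3, 0.05 | 16–26% | 38–54% |
| 4, 0.05 | 24–43% | 52–73% |
| 3, 0.025 | 9–16% | 27–42% |

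**Step 5: three arms with the test the protocol names.** A separate simulation used other assumed distributions, with both devices shifted by an odds ratio of 3, and compared chi-square with Kruskal-Wallis. Seven spread levels: 23% against 55%. Five equal levels: 32% against 54%. Bleeding with 70% having none: 10% against 32%. The pattern is the same.

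**The case against.** The strongest reply is that the protocol does not fix a wrong test. The sentence on chi-square follows one that names Kruskal-Wallis, which respects order and can take grades. A statistician could treat the grades as nonparametric data within the existing wording. This stands. A reader might infer that chi-square is the only test the plan offers for these outcomes, but the Statistical design section does not support that. What remains is that the section has no ordinal category, and its plain wording points graded data to chi-square.

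It can also be said that assigning tests to secondary endpoints is work for an analysis plan, which is not shown. That is fair, and it lowers the priority. It does not remove the point, because the article states a rule for categorical data that would apply to these endpoints as worded.

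A third reply is that the figures are assumed. The number and order of the grades come from the cited grading and are not given in the article. The distributions are invented, and a common odds ratio favours a rank test. An effect that raised some grades and lowered others without a consistent direction could suit the unordered test better. This also stands, and it is why ranges are given.

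Two further inferences go too far. A reader might conclude that the trial's claim about patient outcome and safety rests on these two endpoints. The abstract's discussion names neither and speaks of blood loss; the abstract's list of secondary endpoints omits both; and the section on safety objectives relies on adverse event reporting. A reader might also conclude that a rank test would make a severity shift reliably visible. At an odds ratio of 3 it would still miss about half of such shifts (46 to 62%), so a non-significant result would not show equal safety under either test.

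**Conclusion.** The point holds as a minor one. On its plain reading the protocol compares two graded secondary endpoints with a test that ignores severity order, while also naming a rank test and not saying which applies. If the grades are ordered and a device shifts them consistently, the rank test has about two to three times the power of the unordered chi-square at 23 per arm: 38 to 54% against 16 to 26% at an odds ratio of 3, and about 19 to 25% against 7 to 12% at an odds ratio of 2. These figures depend on the assumed grade distributions and the common odds ratio. The direction was the same in every shifted scenario tried. Neither endpoint is one the trial was sized for, power stays modest with either test, and the primary analysis of blood loss is unaffected.

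**What to change.** In Statistical design, make two changes:

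1. Limit the chi-square test to unordered or binary data.
2. State that graded postoperative bleeding and morbidity, taken as the highest grade per patient with no complication as the lowest level, are compared by a rank test. This can be the Kruskal-Wallis test already named, or Wilcoxon rank-sum tests of each device against control, which would match the two contrasts in the Hypotheses section.

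Show the table of grades by arm alongside. A common odds ratio from a proportional-odds model, with its confidence interval, is an optional addition; it assumes a similar shift across grades and is less familiar to surgeons than a percentage, and the grade table covers both drawbacks.

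The cost is one or two sentences. No new data, patients or staff are needed.

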#### Ethical and legal aspects

##### Ethical basics

The study protocol is in accord with the 2013 version of the Helsinki declaration. Participants will voluntarily enroll in the study; consent may be withdrawn at any time, without giving reasons and without disadvantages for further medical care. Execution of the trial is to be carried out by the KSC, an internal division of the Department of General, Visceral, and Transplantation Surgery of the University Hospital Heidelberg. Study personnel will not be additionally compensated for execution of the trial. There is no restricted external financial support for the trial. Participants in the trial will not be compensated financially or otherwise. Because the entire trial will incorporate fully licensed and approved methods in the regular treatment course, no additional compensation for harmful outcomes will be provided.

#### Patient information/informed consent

Patients will be informed in writing and verbally about the nature and scope of the planned study before the start of the study, in particular about the possible benefits to their health and potential risks. Patient approval will be documented by the patient’s signature on the informed consent form. Upon resignation from the study, either data will be destroyed or the patient will be asked whether he/she agrees with further evaluation of the material collected during the trial.

#### Legal basics

##### Vote of the ethics committee

The study protocol will be submitted for review before the trial’s start date by the ethics committee of the University of Heidelberg’s medical faculty. The study will not begin until a written vote from the ethics committee has been received. All relevant changes to the trial protocol will be announced to the ethics committee.

#### Data protection/insight into original patient records

The names of the patients and all other confidential information will be subject to medical confidentiality and the provisions of the German Federal Data Privacy Law (Bundesdatenschutzgesetz [BDSG]) and the European Union General Data Protection Regulation. Transfer of patient data is only possible in pseudonymized form. Third parties will not have access to the original patient records.

## Trial status

The latest protocol version of the SEALIVE trial is version 1.6 (June 16, 2018). Recruitment of patients was planned to begin in July 2018.

## Abbreviations

BL: Blood loss
CRF: Case report form
CVP: Central venous pressure
FFP: Fresh frozen plasma
Hb: Hemoglobin
INR: International normalized ratio
ITT: Intention to treat
IVC: Inferior vena cava
KSC: Clinical trial center (Klinisches Studien Centrum)
LS: LigaSure™
LT: Liver transplant
POD: Postoperative day
PRBC: Packed red blood cells
PTT: Partial thromboplastin time
SAE: Serious adverse event
TEAE: Treatment-emergent adverse events
USD: Ultrasonic dissector
